## Procedure for Obtaining Informed Consent

1) Prior to the beginning of the trial, the principal investigator or subinvestigator will fully inform the patient or his/her legally acceptable representative of all pertinent aspects of the trial, presenting the informed consent form approved by the Institutional Review Board. Clinical research coordinators may assist in providing the information. The information will be provided in accordance with the informed consent form for this trial, using language as simple as practical to make sure that the patient or his/her legally acceptable representative understands it. Questions from the patient or his/her legally acceptable representative about the trial will be thoroughly answered. Upon confirmation that the patient or his/her legally acceptable representative well understands the information, a written voluntary consent to participation in the trial shall be obtained from the patient or his/her legally acceptable representative.

2) The informed consent form will be signed or have name seal affixed, and be personally dated by the principal investigator or subinvestigator who conducted the informed consent discussion, and by the patient or his/her legally acceptable representative. The clinical research coordinator who assisted in providing the information will also sign or affix their name seal, and personally date the form, if applicable.

3) The principal investigator or subinvestigator will deliver the signed/sealed and dated informed consent form to the patient or his/her legally acceptable representative prior to the patient’s participation in the trial. The original informed consent form will be stored appropriately in accordance with the policy of the institution.

4) Considering that the target population for the trial ranges from patients aged seven to forty nine years, an informed consent form concerning an underage patient, i.e., under twenty years of age, shall be accompanied by a written consent from the patient’s legally acceptable representative, who has been fully informed about the trial, along with reference to the informed consent form. The principal investigator or subinvestigator will also provide an explanation to the patient in plain language, and obtain written informed consent from the patient as far as practical.

## Revision of the Informed Consent Form

1) The principal investigator will determine in a timely manner whether the informed consent form requires any revision whenever important new information becomes available that may be relevant to the subjects’ consent.

2) If the principal investigator recognizes the need for revision, the informed consent form will be revised in a timely manner and receive renewed approval by the Institutional Review Board.

3) When a case to which 2) above, applies arises, the principal investigator or subinvestigator will inform the subjects already participating in the trial or their legally acceptable representatives orally of the situation without delay, ascertain whether the subjects are willing to continue their participation in the ongoing trial, and record the responses in subjects’ clinical records.

4) The principal investigator or subinvestigator shall provide an explanation to the subjects already participating in the trial or their legally acceptable representatives using the revised informed consent form approved by the Institutional Review Board, and obtain written voluntary consent from the subjects or their legally acceptable representatives in regard to subjects’ continued participation in the trial.

5) The principal investigator or subinvestigator, and the subject or his/her legally acceptable representative will sign/seal and personally date the consent form in the same manner as the initial consent. The clinical research coordinator who assisted in providing the information will also sign or affix their name seal, and personally date the form, where applicable.

6) The principal investigator or subinvestigator will deliver the signed/sealed and dated informed consent form to the subjects or their legally acceptable representatives. The original informed consent form will be stored appropriately in accordance with the policy of the institution.

# Investigational Products

## Brief Description of the Investigational Products

1) Test drug

(1) Product name: NPC-12T active substance tablets

(2) Ingredients: Sirolimus

(3) Dosage form: White, sugar-coated tablets containing sirolimus 1 mg each

(4) Storage: Stored in airtight containers, at ambient temperature, and away from light.

2) Comparator

(1) Product name: NPC-12T placebo tablets

(2) Dosage form: Tablets containing excipients identical to those of the active substance NPC-12T, but not containing sirolimus

(3) Storage: Stored in airtight containers, at ambient temperature, and away from light.

## Packaging and Labeling

The investigational product provider shall package and label the investigational products in the following manner for delivery to the storage manager(s) of the institution:

1) Packaging

<Phase I: Single-blind trial>

NPC-12T placebo tablets will be packaged in PTP (push-through-pack) sheets, with each sheet containing 10 tablets. A set of 10 PTP sheets will be wrapped in a transparent pillow package, which is then to be unit boxed and sealed.

<Phase II: Double-blind trial>

Test drug (silorimus): NPT-12T active substance tablets will be packaged in PTP sheets, with each sheet containing 10 tablets. A set of 10 PTP sheets will be wrapped in a transparent pillow package, which is to be unit boxed and sealed. Eight unit boxes will be packed in one inner carton.

Comparator (placebo): NPT-12T placebo tablets will be packaged in PTP sheets, with each sheet containing 10 tablets. A set of 10 sheets will be wrapped in a transparent pillow package, which is to be unit boxed and sealed. Eight unit boxes will be packed in one inner carton.

One set of investigational products dispensed to each subject will be put together in one master carton, which will consist of two unit boxes of Phase I placebo (200 tablets in total) and one inner carton of Phase II test drug or comparator (eight unit boxes containing 800 tablets in total).

2) Labeling

The labels on individual packets and unit boxes will explicitly indicate “for clinical trial use only,” and include at least the following information:

・That the products are solely for clinical trial use

・Code number of a treatment assignment

・The name, title, and address of the principal investigator

・Identification number

・Manufacturer’s serial number

・Storage

・Quantity

・Expiration

Unit boxes, inner cartons, and master cartons should be labeled as shown below.

The corner mark on the top right corner indicates the position where code number stickers should be placed.

(1) Unit boxes for Phase I

| For clinical trial use only Phase I NPC-12T tablets  Protocol Number: KCTR-D012  Manufacturer’s Serial Number: NP12T17X1  Storage: at room temperature  Quantity: 100 tablets (10 sheets)  Expiration: as prescribed in the policy on expiration of the investigational products  Principal investigator: [name], PhD, Assistant Professor, Keio University School of Medicine  [name]  Note: The box and unused drugs are to be collected. Please do not discard. |
| --- |

(2) Unit boxes for Phase II (test drug and comparator)

| For clinical trial use only Phase II NPC-12T tablets  Protocol Number: KCTR-D012  Manufacturer’s Serial Number: NP12T17X1  Storage: at room temperature  Quantity: 100 tablets (10 sheets)  Expiration: as prescribed in the policy on expiration of the investigational products  Principal investigator: [name], PhD, Assistant Professor, Keio University School of Medicine  [name]  Note: The box and unused drugs are to be collected. Please do not discard. |
| --- |

(3) Inner cartons for Phase II (containing eight unit boxes)

| For clinical trial use only Phase II NPC-12T tablets  Protocol Number: KCTR-D012  Manufacturer’s Serial Number: NP12T17X1  Storage: at room temperature  Quantity: 800 tablets (8 unit boxes)  Expiration: as prescribed in the policy on expiration of the investigational products  Principal investigator: [name], PhD, Assistant Professor, Keio University School of Medicine  [name]  Note: The box and unused drugs are to be collected. Please do not discard. |
| --- |

(4) Master boxes for individual subjects (containing two unit boxes for Phase I and one inner carton for Phase II)

| For clinical trial use only NPC-12T tablets  Protocol Number: KCTR-D012  Manufacturer’s Serial Number: NP12T17X1  Storage: at room temperature  Quantity: 2 unit boxes for Phase I and 8 unit boxes for Phase II  Expiration: as prescribed in the policy on expiration of the investigational products  Principal investigator: [name], PhD, Assistant Professor, Keio University School of Medicine  [name]  Note: The box and unused drugs are to be collected. Please do not discard. |
| --- |

## Handling of the Investigational Products

The principal investigator will procure investigational products after two weeks or later from the conclusion of the agreement with the investigational product provider regarding provision of the investigational products and the submission of the protocol. The investigational product storage manager will store and manage the investigational products in accordance with the Procedures for the Management of the Investigational Products developed by the principal investigator. After the end of the trial, the storage manager will dispose of any unused products appropriately and document the fact.

The investigational products shall not be used for any purposes other than this clinical trial.

# Procedures of the Trial

## Registration of Patients

The principal investigator or subinvestigator will obtain written informed consent from patients who are thought to satisfy the inclusion criteria, or their legally acceptable representatives, and register the patients in accordance with the following procedures:

| 1) Selection of patients | |
| --- | --- |
|  | The principal investigator or subinvestigator will carefully examine whether respective patients are eligible to participate in the clinical trial, taking account of patients’ health conditions, symptoms, age, gender, relationship with the principal investigator, and participation in any other clinical trials. |
| 2) Informed consent | |
|  | The principal investigator or subinvestigator will provide information pertinent to the clinical trial to patients who are thought to satisfy the inclusion criteria of the trial, and obtain written informed consent from the patients or their legally acceptable representatives. |
| 3) Assignment of subject identification code | |
|  | Subsequent to informed consent, required data will be entered into the electronic case report forms, and subject identification code numbers will be assigned. This will be recorded on the subject screening list. The code numbers will be used for identification of the patients throughout this trial. |
| 4) Screening | |
|  | Patients will go through screening two weeks (+/- seven days) before the initial intake of the investigational products. |
| 5) Confirmation of eligibility by the principal investigator or subinvestigator | |
|  | Prior to starting the first dose of the investigational products, the principal investigator or subinvestigator will judge whether patients satisfy the inclusion criteria, based on the assessment during the screening phase, using the eligibility check sheet. |
| 6) Registration of subjects and assignment of investigational products (V1) | |
|  | Patients whose eligibility to participate in the trial is confirmed in 5) will be registered and have investigational products assigned via the electronic case report form. Unique code numbers (pharmaceutical agent numbers) will be assigned to the registered subjects. This will be recorded in the subject screening log.  Patients whose eligibility is denied in 5) will be treated as screen failures. Screen failures will be recorded in the remarks column of the subject screening log. |

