# Study Plan

## Schedule of Activities

Table 1 shows the procedures and schedule of the trial.

Table 1 Procedures and Schedule

|  | Screening | Phase I (3 months) | | | | Phase II (6 months) | | | | | | | | Follow-up | Discontinuation |
| --- | --- | --- | --- | --- | --- | --- | --- | --- | --- | --- | --- | --- | --- | --- | --- |
| **Visits** | Visit 0 (V0) | V1 | V2 | V3 | V4 | V5^1,2^ | V6^2^ | V7^2^ | V8 | V9 | V10 | V11 | V12 | V13 |  |
| **Days/Week** | -2W | D1 | 2W | 4W | 8W | 12W | 14W | 16W | 20W | 24W | 28W | 32W | 36W | 40W |  |
| **Allowable visit windows (days)** | +/-7 | 0 | +/-3 | +/-3 | +/-7 | +/-3 | +/-3 | +/-3 | +/-7 | +/-7 | +/-7 | +/-7 | +/-7 | +/-7 |  |
| In-clinic visits | X | X | X | X | X | X | X | X | X | X | X | X | X | X | X |
| Informed consent | X |  |  |  |  |  |  |  |  |  |  |  |  |  |  |
| Eligibility judgment, random assignment, and prescription of investigational products | | | | | | |  |  |  |  |  |  |  |  |  |
| Eligibility judgment | X | X |  |  |  |  |  |  |  |  |  |  |  |  |  |
| Registration and assignment |  | X |  |  |  |  |  |  |  |  |  |  |  |  |  |
| Prescription of investigational products |  | X | X | X | X | X^1^ | X | X | X | X | X | X |  |  |  |
| Prior medication review |  | X | X | X | X | X | X | X | X | X | X | X | X |  | X |
| Tests to be carried out at subjects’ homes | | |  |  |  |  |  |  |  |  |  |  |  |  |  |
| Instructions on the portable test devices / ePRO | X |  |  |  |  |  |  |  |  |  |  |  |  |  |  |
| Test using the portable devices and ePRO input (at patients’ home) |  |  |  |  |  |  |  |  |  |  |  |  |  |  |  |
| Collection of data from portable devices and ePRO |  | X | X | X | X | X | X | X | X | X | X | X | X | X | X |
| Collection of the portable devices and ePRO |  | X^3^ |  |  |  |  |  |  |  |  |  |  |  | X | X |
| In-hospital tests and observation | |  |  |  |  |  |  |  |  |  |  |  |  |  |  |
| Medical interview on dizziness | X | X | X | X | X | X | X | X | X | X | X | X | X | X | X |
| Thoracic X-ray | X |  |  |  |  |  |  |  |  |  |  |  |  |  |  |
| Pure-tone audiometry | X | X |  | X | X | X |  | X | X | X | X | X | X | X | X |
| Auditory brainstem response | X |  |  |  | X |  |  |  |  |  |  |  | X |  | X |
| Posturography | X | X |  | X | X | X |  | X | X | X | X | X | X | X | X |
| Carolic and c-VEMP tests | X |  |  |  |  | X |  |  |  |  |  |  | X |  | X |
| Speech audiometry | X |  |  |  | X |  |  |  |  |  |  |  | X | X | X |

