# Administration of Investigational Products

Figure 1 Dosing Protocol

Phase I (single-blind): NPC-12T placebo tablets for 3 months (12 weeks)

Phase II (double-blind): NPC-12T active substance tablets or NPC-12T placebo tablets for 6 months (24 weeks)

[Dosage at the outset of the trial]

Subjects weighing less than 40 kg will take one 1-mg tablet orally once every other day.

Subjects weighing 40 kg or more will take one 1-mg tablet orally once per day.

The investigational products are to be taken before sleep.

The bodyweight measured at V1 will be referred to in determining dosage throughout the trial.

<Rationale for the dosing time>

The package insert of Rapamune 1 mg tablets was referred to when setting the dosing time. The insert cites reports that state administration of the tablet after a high-fat meal increased the blood concentration of sirolimus. To reduce effects of high-fat meals, the dosing time of the investigational products is set to be before sleep.

[Prescription of the investigational products]

In Phase I (V1, V2, V3, and V4) and Phase II (V5 and V6), the principal investigator or subinvestigator will prescribe investigational products in accordance with the dosage at the start of the trial described above.

In Phase II (V7, V8, V9, V10, and V11), the unblinded doctor will instruct the principal investigator and subinvestigators on the prescription of the investigational product based on the criteria for dosage change. The principal investigator or subinvestigator will make a judgment on whether dosage reduction is required or dosage increase is permissible, taking account of subjects’ safety, including risks of adverse events. If the conditions are deemed appropriate, the principal investigator or subinvestigator will prescribe the investigational products as instructed by the unblinded doctor. The unblinded doctor will provide instructions to the principal investigator or subinvestigator in accordance with the trough concentration measurements and the prescription schedule generated by the randomization manager. The trough concentration measurements and the prescription schedule are not to be disclosed to any person except the unblinded CRCs until the end of the trial, and will be kept securely locked in a cabinet accessible only to the unblinded doctor.

[Criteria for dosage change]

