From Phase II, the dosage will be determined taking account of the trough concentration measurements from the last visit (V6, V7, V8, V9, and V10) and occurrence of adverse events.

The unblinded doctor will provide instructions to the principal investigator or subinvestigator on prescription of the investigational products based on the trough concentration measurements at visits.

The principal investigator or subinvestigator will make a judgment on whether dosage reduction is required or dosage increase is permissible before prescribing, with due consideration for the subjects’ safety, such as risks of adverse events.

In this trial, the therapeutic range of the trough concentration following the administration of NPC-12T active substance is set to be 2.5 to 7.5 ng/mL. The trough concentration at the last visit below 2.5 ng/mL will be considered to be suitable for dosage increase, and that exceeding 7.5 ng/mL for dosage reduction.

Dosage increase for NPC-12T active substance will be permitted only if the principal investigator or subinvestigator deems it appropriate from the viewpoint of subject safety. The unblinded doctor will instruct the principal investigator or subinvestigator to prescribe the investigational products not exceeding two 1-mg tablets per day (i.e., 2 mg/day), administered orally.

The reduced dosage of NPC-12T active substance should be no less than one 1-mg tablet every three days, administered orally. If further reduction is required, administration of the investigational product to the subject will be discontinued.

As dosage adjustment according to trough concentration is unsuitable for the NPC-12T placebo arm, one of increase, reduction, or no change in dosage is specified for the placebo arm at the time of assignment of the investigational products. At the same time, the randomization manager will designate the visits for dosage change for the placebo arm.

Dosage increase for NPC-12T placebo will be permitted only if the principal investigator or subinvestigator deems it appropriate from the viewpoint of subject safety. When dosage increase is specified in the prescription schedule, the unblinded doctor will instruct the principal investigator or subinvestigator to prescribe a dosage level at one tier higher.

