# Statistical Analyses

## Populations for Analyses

### Analysis Sets

[Safety]

The safety analysis set will include a set of subjects to whom the investigational products had been administered at least once.

[Efficacy]

1) Full Analysis Set (FAS)

The full analysis set (FAS) will be based on the intention-to-treat (ITT) principle, and will include all patients in this trial other than those who fall under any of the following conditions:

・Violation of eligibility criteria (patients who do not meet main registration criteria for this trial)

・Patients in whom the investigational products had never been administered

・Non-existence of baseline nor treatment data

・Withdrawal of consent during the trial and refusal to allow use of all data

2) Per Protocol Set (PPS)

The Per Protocol Set will include a set of subjects who meet the eligibility criteria for the efficacy analysis based on the standards for subject analysis sets developed before database locking. Eligibility criteria for data to be measured chronologically shall be specified for individual points in time for measurement.

The main analysis set for efficacy in this trial is to be the FAS. For main efficacy endpoints, statistical analysis of the PPS will also be performed. Comparison of the results of two distinctive analysis sets will be used to evaluate the robustness of main analysis results of the trial.

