## Target Study Sample Size

A sample size of 16 subjects is expected to be studied: 12 subjects for NPC-12T active substance arm, and 4 subjects for NPC-12T placebo arm.

[Reason for choice of sample size]

As this clinical trial will focus on a rare disease, and is exploratory, feasibility was the main aspect that was considered in setting the sample size. In terms of safety analysis, provided that clinically significant adverse events exist, the size is sufficient to detect adverse events of 15% incidence with 85% accuracy. In terms of efficacy analysis, when making a comparison of NPC-12T arms concerning hearing test endpoints of periods without treatment and with treatment, a difference can be detected at 80% power (two-sided 5% significance level), if the number of evaluable subjects is 11 and Cohen’s d for endpoints is 0.85.

In estimation of correlation coefficient between evaluation indices, if data of two arms are integrated for evaluation, and the number of evaluable subjects having population correlation coefficient of 0.7 (i.e., medium to high degree of correlation) is 13, then a difference can be detected at a minimum of 80% power (two-sided 5% significance level).

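### Neither the safety set nor, read literally, the FAS requires a Phase II dose, so a subject assigned to sirolimus at V1 who took only run-in placebo can enter the by-arm safety denominator

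*Protocol*

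**What the plan says.** **Assignment.** Protocol 10.1, step 6, is headed "Registration of subjects and assignment of investigational products (V1". The row "Registration and assignment" in the Schedule of Activities is marked at V1 only.

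**Treatment.** Section 11 gives "Phase I (single-blind): NPC-12T placebo tablets for 3 months (12 weeks" and then "Phase II (double-blind): NPC-12T active substance tablets or NPC-12T placebo tablets for 6 months (24 weeks". Phase II starts at V5, week 12.

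**What is settled at assignment.** Under 9.2 each subject's master carton holds "two unit boxes of Phase I placebo (200 tablets in total) and one inner carton of Phase II test drug or comparator". Under section 11, "one of increase, reduction, or no change in dosage is specified for the placebo arm at the time of assignment of the investigational products".

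**Analysis sets (17.1.1).** The safety set is "subjects to whom the investigational products had been administered at least once". The FAS removes subjects who violate eligibility, were never dosed, lack baseline and treatment data, or withdraw consent and refuse use of their data. Neither definition mentions Phase II.

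**Safety analysis.** Adverse events count from the first dose at V1 through V13 (14.10.1). Incidence is reported by dosing arm with Clopper-Pearson intervals (17.4.1), without a split by phase. Adverse events are the first primary endpoint.

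**Size.** Section 17.5 plans "12 subjects for NPC-12T active substance arm, and 4 subjects for NPC-12T placebo arm" and says this suffices to detect a 15% adverse event with 85% accuracy.

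**The concern.** Section 9.1 lists the placebo tablets as one of the two investigational products, so a single Phase I tablet satisfies the safety-set rule. A subject assigned to sirolimus who leaves in week 4, say, has an arm label and a place in the safety set, but has never taken sirolimus. If the arm label decides where that subject is counted, the active-arm denominator contains someone who could not have had a sirolimus reaction. In an arm of 12, one such subject is 8.3% of the denominator of the primary endpoint.

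If dosing arm instead means product received, the same subject joins a placebo arm planned at 4, having taken only run-in treatment. The protocol does not say which meaning applies.

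The FAS has the same gap. Its dosing exclusion covers only subjects never dosed. Its data exclusion, read literally, requires both baseline and treatment data to be missing, so a run-in dropout with baseline data stays in.

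**Working it through.** **Inputs.** From 17.5: 12 active subjects, 4 placebo subjects, a 15% event rate and an 85% chance of detection. The protocol states no run-in dropout rate, so the rates in step 4 are assumptions.

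**1. The plan's own figure.** Take detection to mean at least one event among n exposed subjects: P = 1 − 0.85^n.
- n = 12: 1 − 0.85^12 = 85.8%, which reproduces the stated 85%.
- n = 16: 1 − 0.85^16 = 92.6%, which does not.

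The stated figure therefore fits 12 subjects who actually receive sirolimus.

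**2. Fewer exposed subjects.**
- 11 exposed: 1 − 0.85^11 = 83.3%
- 10 exposed: 1 − 0.85^10 = 80.3%

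**3. Dilution of the reported rate.** Suppose k of the 12 took only Phase I placebo, are counted as active and have no such event. The expected reported rate is 0.15 × (12 − k)/12.
- k = 1: 0.15 × 11/12 = 13.8%
- k = 2: 0.15 × 10/12 = 12.5%

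**4. How often this could arise.** With run-in loss q per subject, the chance that at least one of 12 active-assigned subjects leaves in Phase I is 1 − (1 − q)^12. The chance of two or more is 1 − (1 − q)^12 − 12q(1 − q)^11.

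| Assumed q | At least one of 12 | Two or more of 12 |
| --- | --- | --- |
| 3% | 31% | 5% |
| 5% | 46% | 12% |
| 10% | 72% | 34% |

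These figures show how often the definition would matter. They do not measure a loss caused by assigning at V1: if 16 enter and one leaves in the run-in, 15 reach V5 whenever assignment takes place.

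**5. Does run-in loss depend on arm?** Allocation is concealed, and all subjects take the same placebo in Phase I. Under 10.2 the unblinded doctor opens a subject's prescription schedule when judging dose changes, at V7 to V11. Nothing in Phase I gives one arm a reason to lose more subjects than the other.

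**The case against.** The strongest reply is that 17.1.1 says who enters the safety set, not which arm they count in. Section 17.4.1 does not define dosing arm as assigned or received. The FAS data exclusion can also be read as removing run-in dropouts, and 17.1.2 and 17.9 leave detailed standards and data handling to be settled before lock and unblinding. This is fair, and it makes the dilution conditional on how the subject is counted. It does not remove the point: the entry rule is fixed in the protocol, admits the subject as written, and gives no sound place to count that subject in a by-arm table.

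The second reply is about size: the dropout rate is unknown, the trial is exploratory, and one lost active subject moves the detection chance by 2.5 points (85.8% to 83.3%). This also stands, and it keeps the point modest.

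A reader might infer more, namely that assigning at V1 is itself a mistake. The documents do not support that:
- Concealment and identical Phase I treatment mean that no selection bias is expected.
- Moving assignment to V5 does not by itself save places, as step 4 of the working shows.
- Assignment at V1 is consistent with the supply and blinding arrangements: the master carton, the coded unit boxes, the emergency key codes and the sealed prescription schedules.
- Run-in dropouts assigned to placebo did take placebo, though not their Phase II course. Only those assigned to sirolimus never receive their assigned product.

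**Conclusion.** The point holds as a fault in the analysis-set definitions. Because assignment precedes the first difference between arms by 12 weeks, the at-least-once rule admits subjects who took only run-in placebo, and neither set is tied to a Phase II dose. For the safety set this follows directly from the text. For the FAS it rests on the literal reading of the data exclusion.

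Per active-assigned run-in dropout, a true 15% rate appears as 13.8%, and the chance of seeing such an event is 83.3% rather than 85.8%. The 13.8% assumes that the subject is counted in the assigned arm and has no such event in Phase I. The 83.3% needs only that 11 rather than 12 receive sirolimus. How often this happens is unknown, because no dropout rate is stated. The point concerns the primary endpoint and is cheap to correct, but it does not threaten the validity of the randomised comparison.

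**What to change.** **Definitions in 17.1.1 and 17.4.1**
- FAS: add the requirement of at least one Phase II dose.
- Between-arm safety set: subjects with at least one Phase II dose. State whether dosing arm means assigned or received product.
- Phase I adverse events: report separately, for all subjects dosed in Phase I.

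**Cost.** Two sections change, with no new data collection and no change to supplies. The analysed number may fall slightly below the number randomised. This should not bias the comparison, since the subjects removed left before the arms differed. The change removes the dilution but does not restore lost exposure: with 11 exposed, the detection chance stays at 83.3%.

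**Option for the sponsor.** Where supply allows, randomise at V5. This changes the coded unit boxes, the master cartons, the emergency key codes and the timing of the prescription schedules. It keeps 12 + 4 only if more subjects enter the run-in: 16/0.95 = 16.8, so 17, at an assumed 5% loss, or 16/0.90 = 17.8, so 18, at 10%. In a rare disease, where feasibility set the sample size, that recruitment is a real cost.
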